##### Data collection procedures:

We will determine the daily case counts for ***community SARS-CoV-2 data*** using the JHU Coronavirus Resource Center for each selected county [1]. The daily case count data are made publicly available by the COVID-19 Data Repository operated by the Center for Systems Science and Engineering (CSSE) at JHU [21]. Documentation of the data by JHU is available at https://github.com/CSSEGISandData/COVID-19. This website contains a complete list of all sources used in the COVID-19 case data since January 21, 2020. There are 122 data sources for the county-level daily COVID-19 case count data. These data will be obtained through the ‘sars2pack’ R package (https://seandavi.github.io/sars2pack/) created by [name] at the University of Colorado-Anschutz and [name]. The case tracking data used for this study will include the date, count of cases, and the state and county to which the cases belong. We will obtain incidence data temporarily from the JHU source until the data resources on incident cases and other outcomes from the state health departments are successfully established.

The Google ***mobility data*** will be used to examine workplace, retail, grocery, and residential mobility. We defined workplace, retail, and grocery mobility as the number of visits to locations of each type; residential mobility is the duration of time spent at residential locations. The daily percentage change in mobility for each type of outcome is relative to a pre-pandemic baseline from early 2020 and is reported in Google’s COVID-19 Community Mobility Reports [22]. The 7-day average is computed from the daily percentage change for a selected county within a state. Among matched control communities during the study period beginning January 1, 2021, the daily percentage change is missing for approximately 3–11% of county-date pairs for each type of mobility. Excluding communities with > 50% missing values for a given category, the missing proportions are approximately 0–4% for each type of mobility. In these cases, the statewide average change for that day is used to impute the missing data. All mobility outcome values are fully observed for both intervention communities. The pre-pandemic baseline is a set of days representing the normal number of visits to workplace locations for a given day of the week. Therefore, the baseline is made up of seven individual values and is not a single value. The baseline for a particular day of the week is the median value from the 5 weeks from January 3 to February 6, 2020. The daily percentage change for a given day of the week is calculated by comparing the number of visits for the given day with the baseline for that given day.

The Apple mobility outcomes include the number of the driving route and walking route requests on Apple Maps. The daily percentage change in the number of a given type of request (driving or walking) is relative to the number of requests for that type made on January 13, 2020. We will obtain these data from Apple’s Mobility Trends Reports. The data and their documentation are available at https://covid19.apple.com/mobility.

The outcome variable for ***wastewater surveillance*** is normalized SARS CoV-2 concentrations, expressed as viral copies per liter. Twice weekly, 24-h composite wastewater samples are obtained at each sampling location, following the testing laboratory’s recommendations. For the Tennessee sites, the samples are taken according to the protocol and kits provided by Biobot Analytics, Inc., and tested by Biobot [23]; testing began on April 26, 2021. The North Carolina sites are being sampled and assayed under a contract through the CDC National Wastewater Surveillance System, with all the samples processed and assayed through the laboratory of [name] at UNC-Chapel Hill; sample collection is ongoing and started in September 2020. Samples are drawn from all locations on Monday and Thursday. The collection follows a standard 24-h cumulative sampling methodology. Historical biweekly samples and analyses are available from June 2020 through April 2021 for Chattanooga, weekly samples and analyses are available from October 2020 through mid-February 2021 for the MC Stiles facility in Memphis, and twice-weekly samples and analyses for the North Carolina sites will be available from September 2020 through April 2021. For the public health intervention, continuous twice-weekly sampling through the end of August will occur for North Carolina, with a 3-month follow-up after the intervention period. Continuous twice-weekly sampling through the end of September will occur for Tennessee. Analyte testing in North Carolina and Tennessee is performed using qPCR. The analysis reports from Biobot performed on samples collected in the Moccasin Bend Wastewater Treatment Plant in Chattanooga, TN, are publicly accessible at https://connect.chattanooga.gov/covid-biobot-analysis-reports/. These reports are generated and sent to the customer within 48 h of the receipt of the sample. In the analysis, the SARS-CoV-2 viral concentrations are calculated, normalized using internal controls, rainfall, the population covered by the sewer shed, and wastewater flow data.

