We will use mixed modeling techniques to compare trends over time between intervention and control communities. Specifically, for each outcome and intervention/control community matched pair, a generalized linear model of 7-day average or twice-weekly outcomes by community and time with a time-by-community interaction will be fit, adjusted for vaccination coverage and the percentage of SARS-CoV-2 cases attributable to the B1.1.7 variant. Correlated residuals will be modeled within a community with an autoregressive correlation structure. The community will be modeled with a categorical fixed effect. Time will be modeled using restricted cubic splines. Four knots will be considered: at the beginning, at the transition from one period to the next, and at the end. Piecewise linear splines by period will also be considered for adequate fit. Linear time-by-community interactions will be included for each time. Vaccination coverage and percent of SARS-CoV-2 cases attributable to the B1.1.7 variant (estimated from wastewater data) will be modeled as a time-varying covariate where available, transformed as needed. The appropriate distribution and respective canonical link function will be used for each outcome type on the multiplicative/log scale when possible—i.e., binomial if a proportion, Poisson if discrete, log-transformed, and normal if continuous. Each intervention community will be compared to each matched control community separately within the intervention periods. This will be done by comparing the appropriate time-by-community interaction parameters using a likelihood ratio test with alpha = 0.05. This analysis will be repeated for the wastewater viral concentrations data.

Trends in mobility outcomes should be interpreted with caution. The outcome will reflect trends on the day of the week not corrected by the baseline value. The analytic team will consider smoothing methods to mitigate this effect.

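### Missing Google mobility days in control counties are filled with the raw statewide value, which can distort the trend comparison in an individual pair; the county's own offset from the state should be added

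*Protocol article*

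**What the plan says.** The rule is in the protocol article under Data collection procedures, in the paragraph on Google mobility. Among the matched controls, "the daily percentage change is missing for approximately 3–11% of county-date pairs for each type of mobility". The next sentence reports that "Excluding communities with > 50% missing values for a given category, the missing proportions are approximately 0–4% for each type of mobility". The rule follows: "In these cases, the statewide average change for that day is used to impute the missing data". No adjustment to the county's own level is stated. The sentence also leaves unclear whether the fill applies only to the retained communities or also to those above the 50% cut.

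On the intervention side, "All mobility outcome values are fully observed for both intervention communities".

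The imputed days feed the analysed series: "The 7-day average is computed from the daily percentage change for a selected county within a state". Under Analysis plan, these averages enter a model with a categorical fixed effect for community and time-by-community interactions. "Each intervention community will be compared to each matched control community separately within the intervention periods", by "comparing the appropriate time-by-community interaction parameters using a likelihood ratio test with alpha = 0.05". That section advises caution on mobility trends, but the reason given is day of week, not imputation.

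**The concern.** A county's mobility change can sit persistently above or below its state's. Study sites says that no control was likely to match on every factor, and mobility is only one of the matching categories, so some controls may differ from the state by several points. On each imputed day such a control leaves its own level and takes the state's. The intervention series never does this.

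The pooled 0–4% does not bound what happens in one county. The only stated limit per county is the 50% cut, and each control is compared on its own, so a sparse county is not diluted by the others. If its missing days fall mostly in one period, the step between county level and state level can look like a change in mobility in the control. In the comparison it would then appear as an intervention difference of the opposite sign.

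**Working it through.** **Inputs from the protocol article.** Missing share 3–11% over all controls and 0–4% after exclusion; exclusion above 50%; 7-day averages; pre-intervention from January 1, 2021 to kit distribution (April 4, 2021 in Pitt County, 93 days); intervention 11–12 weeks (84 days used); post-intervention 90 days. Total 93 + 84 + 90 = 267 days.

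**Assumed, because the article does not give them.** The gap d (statewide minus county change) at 5, 10 or 20 percentage points, and the timing of the missing days.

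**The stated percentages.** They are counts from data not shown and cannot be reproduced, but they can be checked for coherence. Share of communities excluded = (overall − kept)/(m − kept), where m is the missing share in the excluded communities, taken from 50% to 100%. Pairing the upper ends: (0.11 − 0.04)/(0.50 − 0.04) = 15% down to (0.11 − 0.04)/(1 − 0.04) = 7%. Pairing the lower ends: 0.03/0.50 = 6% down to 0.03/1 = 3%. The figures are plausible.

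**Level shift = missing share × d.**
- At 4%: 0.04 × 5 = 0.2, 0.04 × 10 = 0.4, 0.04 × 20 = 0.8 points.
- For a retained county at the 50% limit: 2.5, 5 and 10 points. At a pooled 4%, at most 0.04/0.50 = 8% of retained series could be there, and only if all the others were complete.

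**Shift in one 7-day average = (k/7) × d, with k imputed days.** At d = 10: k = 1 gives 1.4, k = 2 gives 2.9, k = 7 gives 10 points.

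**Effect on trend.** This was simulated with 400 runs per pattern on the 267-day Pitt timeline, with d = 10. Piecewise-linear slopes by period were fitted by least squares to the 7-day averages, and the filled control series was compared with the same series fully observed. This is simpler than the planned model, with no autoregressive residuals, so it shows bias in the slope and not the error rate of the planned test. Mean false slope in the intervention period, in points per 30 days:

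| Missing days | 4% | 11% | 50% |
|---|---|---|---|
| Uniform | 0.01 | 0.01 | 0.00 |
| Weekend | 0.02 | −0.01 | 0.00 |
| Rising over time | 0.11 | 0.25 | 1.16 |
| Spread within the intervention period | 0.07 | 0.16 | not run |
| One block at the end of that period | 0.98 | 2.01 | not comparable (block runs into the earlier period) |

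When 4% of all days are missing and all fall within the intervention period, that period's mean moves by about 1.3 points, which agrees with 0.04 × 267/84 × 10 = 1.27. The slopes before and after it move by +0.38 and −0.47. Under uniform missingness the mean bias is about zero, but single series scatter with a standard deviation of 0.17 (4%) to 0.47 (50%) points per 30 days. With no level gap but a state trend 1 point per 30 days steeper, 4% uniform missingness adds 0.04.

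**With the county's mean offset added** (parallel trends assumed): the overall level bias is within 0.01 point and the slope bias within about 0.02 point per 30 days in every pattern tried, at 4%, 11% and 50%.

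**The case against.** The strongest reply is that the tested quantity is a time-by-community interaction in a model that already carries a fixed effect for each community. If missingness is steady, the shift is close to constant and does not enter the contrast. The simulation bears this out. A material false trend needs missingness that changes or clusters over time, or a state trend that diverges from the county's, and the article reports neither. At the stated 0–4% the average shift is below 1 point, and no retained county is shown to be near 50%. The raw fill also has a merit: it keeps day-of-week patterns and shocks common to the state. The scope is narrow too: the outcomes are secondary, and Sample size and power calculation calls the analysis strictly descriptive.

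All of this stands, and it limits the point. It does not remove it, because the pooled rate says nothing about a single pair, the interaction is still to be tested at 0.05, and a distorted series misleads in a plot as well.

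Three stronger readings are not supported:
- A reader might infer that one-sided imputation necessarily produces false trend differences. It does not; the timing of the missing days decides.
- A reader might infer that the comparator is contaminated because a statewide figure contains the intervention county. The article does not say how that average is formed, and at 4% imputed with an assumed 10% county share the weight would be 0.04 × 0.10 = 0.4%.
- A reader might infer that the primary case outcome is affected. It is not imputed this way. Mobility is listed as a covariate to consider, but the model under Analysis plan adjusts only for vaccination coverage and the B1.1.7 share.

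**Conclusion.** The point holds as a limited weakness in a stated rule. The raw statewide fill changes control series only and moves a county toward the state level wherever the two differ. Across the retained controls the effect is small: 0.2 to 0.8 points at 4% missing for assumed gaps of 5 to 20 points, largely absorbed when missingness is steady. In an individual pair it can matter: about 1 point per 30 days for a 4% block at the end of the intervention period, or about 1.2 for a county at 50% with missingness rising over time. Both figures assume a 10-point gap. The article documents neither the gap nor the timing, so these results show what the rule allows, not what the data contain. The consequence is confined to the secondary Google mobility outcomes.

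**What to change.** In the Google mobility paragraph under Data collection procedures, replace the rule with the same-day statewide value plus the control county's own mean difference from the state, estimated on that county's observed days. Make the difference weekday-specific only where enough days of that weekday are observed, since sparse counties may not support it. State whether the fill applies to retained communities only. Repeat each pairwise mobility comparison without heavily imputed controls, with the threshold for heavy imputation set before results are seen.

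Averaging only the observed days in each window is not a clear improvement: if the missing days are mostly weekends, it pulls the average toward weekdays, in an outcome for which the plan already warns about day-of-week trends.

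The cost is a little more code and a sentence or two of text, with no new data. Some bias remains where county and state trends are not parallel, and the repeat analysis is there to show whether that matters.

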##### Sample size and power calculation:

We did not perform a formal power calculation since this is an ecological study. We anticipate that approximately 40,000 households in each intervention community (NC and TN) will participate based on test kit availability. Due to the limited number of intervention communities and only observing outcomes at the community level, there is insufficient power to conduct formal hypothesis tests about the effect of the intervention. Therefore, the proposed analysis is strictly descriptive rather than inferential.

##### Analysis plan:

We will conduct analyses using SAS 9.4 (SAS Institute, Cary NC) or R 4.0 with R Studio 1.4 (R-project). Community characteristic summaries will be reported for each community, and specific variables included will be based on American Community Survey data. Categorical variables will be presented as estimates of counts and percentages with their corresponding 90% confidence intervals, and continuous variables as point estimates of the mean with their corresponding 90% confidence intervals. We will also present trends in community policies directed at pandemic control.

We will plot our outcomes of interest over time stratified by the community, delineating the pre-intervention, intervention, and post-intervention periods. Pre-intervention is defined as from January 1, 2021, until the start date of test kit distribution in each community. The total intervention period is approximately 11–12 weeks, defined as the 6-to-7-week period in which test kits are distributed with an additional 4-week period in which testing is implemented within households, plus a 1-week window to capture household delays usage of the kits. The post-intervention period includes the 90 days after the end of the intervention period. Daily outcomes will have 7-day rolling averages plotted over time at each daily time point. The results from wastewater samples are reported twice each week. The results from those samples will be plotted over time with 7-day rolling averages computed from all tests in that window. The plots of outcomes over time will be stratified by each community within a state.

We will use mixed modeling techniques to compare trends over time between intervention and control communities. Specifically, for each outcome and intervention/control community matched pair, a generalized linear model of 7-day average or twice-weekly outcomes by community and time with a time-by-community interaction will be fit, adjusted for vaccination coverage and the percentage of SARS-CoV-2 cases attributable to the B1.1.7 variant. Correlated residuals will be modeled within a community with an autoregressive correlation structure. The community will be modeled with a categorical fixed effect. Time will be modeled using restricted cubic splines. Four knots will be considered: at the beginning, at the transition from one period to the next, and at the end. Piecewise linear splines by period will also be considered for adequate fit. Linear time-by-community interactions will be included for each time. Vaccination coverage and percent of SARS-CoV-2 cases attributable to the B1.1.7 variant (estimated from wastewater data) will be modeled as a time-varying covariate where available, transformed as needed. The appropriate distribution and respective canonical link function will be used for each outcome type on the multiplicative/log scale when possible—i.e., binomial if a proportion, Poisson if discrete, log-transformed, and normal if continuous. Each intervention community will be compared to each matched control community separately within the intervention periods. This will be done by comparing the appropriate time-by-community interaction parameters using a likelihood ratio test with alpha = 0.05. This analysis will be repeated for the wastewater viral concentrations data.

Trends in mobility outcomes should be interpreted with caution. The outcome will reflect trends on the day of the week not corrected by the baseline value. The analytic team will consider smoothing methods to mitigate this effect.

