#### Test distribution

Test kit distribution began in Pitt County on April 4, 2021, and Hamilton County on May 4, 2021. All test kits were stored in Amazon warehouses located near each community. Participants could receive test kits in two ways: online orders or local distribution partners **(**Fig. 5**).**

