#### Statistical considerations and data analysis

##### Outcomes and measures:

The data used to evaluate the impact of SYCT on participating communities will be publicly available, community-level data. The primary outcome is the number of positive SARS-CoV-2 tests per the local health department. The secondary outcomes fall into one of three categories: wastewater (e.g., SARS-CoV-2 viral copies per liter), mobility (e.g., percentage change in requests for driving directions), and other (e.g., hospitalizations attributable to SARS-CoV-2) (Table 2). We will also consider the following covariates: vaccination coverage, mobility data, and percentage of cases attributed to the B1.1.7 variant.

**Table 2 Tab2:** Summary of primary and secondary outcomes for the ecological study of the SYCT program

Outcome Measures	Endpoints	Data source	Unit of observation	Frequency of data collection	Maximum geographic granularity
Primary					
SARS-CoV-2 test results	Community prevalence point estimate and 95% confidence interval; community incidence rate	Local health departments	County	Daily	County
Secondary					
SARS-CoV-2 viral copies per liter	Community transmission	Wastewater	Wastewater treatment plant sewer shed	Twice weekly	Wastewater treatment plant sewer shed
Number of new hospitalizations for COVID-19 disease per day	Hospitalizations	Local health departments	County	Daily	Center
Hospital census	Hospital capacity/Health care utilization	Local health departments	County	Daily	County/ Healthcare center
GPS location and length of stay; requests for driving directions; requests for walking directions	Mobility	Mobile phones (Google and Apple Maps)	County	Daily	City
SARS-CoV-2-positive patients admitted to the ICU	Number of ICU admissions	Local health department	Individual	Daily	Health care Center

*Abbreviation: ICU* Intensive Care Unit

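### Modelling 7-day averages of case counts with autoregressive residuals, with neither distribution nor dispersion fixed, miscalibrates the intervention-versus-control test by an amount that depends on the reading

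*Protocol article*

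**What the plan says.** All of this is in the Protocol article, in the ecological study's statistical section.

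- **Outcome** (Outcomes and measures): "The primary outcome is the number of positive SARS-CoV-2 tests per the local health department". Table 2 lists it as collected daily.
- **Response** (Analysis plan): "a generalized linear model of 7-day average or twice-weekly outcomes by community and time with a time-by-community interaction will be fit".
- **Averaging** (Analysis plan, on plots): "Daily outcomes will have 7-day rolling averages plotted over time at each daily time point". No other 7-day average of daily outcomes is described.
- **Correlation:** "Correlated residuals will be modeled within a community with an autoregressive correlation structure". The order is not given.
- **Distribution:** chosen by outcome type, "binomial if a proportion, Poisson if discrete, log-transformed, and normal if continuous". No dispersion or scale parameter is mentioned.
- **Test:** each intervention community is compared with each matched control through the interaction parameters, "using a likelihood ratio test with alpha = 0.05".

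The section on sample size and power, by contrast, calls the analysis descriptive and says that power is insufficient for formal tests.

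**The concern.** The response, distribution rule, correlation structure and test are all named in one paragraph, and they do not fit together.

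The primary outcome is a count, which points to the Poisson branch. A 7-day average is not an integer count, which points to the log-normal branch. Two analysts could choose differently for the primary outcome, and the consequences differ greatly.

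If the averages overlap, consecutive values share six of their seven days. Smoothing then creates correlation that is not in the epidemic process, and the named structure has the wrong shape for it.

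At stake is the calibration of the main comparison of intervention with control, whether it is read as a test or as an estimate with an uncertainty.

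**Working it through.** The article states no standard error or power for this model, so there is no figure to reproduce.

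**Inputs from the article.** "Test kit distribution began in Pitt County on April 4, 2021, and Hamilton County on May 4, 2021". From 1 January 2021 the pre-intervention period is 31 + 28 + 31 + 3 = 93 days in Pitt County and 93 + 30 = 123 in Hamilton County. "The total intervention period is approximately 11–12 weeks", that is 77–84 days; 80 are used here. The post-intervention period is 90 days. The simulated series has 93 + 80 + 90 = 263 days.

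**Assumptions not in the article.** Averages are rolling in the model as in the plots; autoregressive order 1; 30 or 100 cases a day; daily variance/mean phi from 1 to 50; daily autocorrelation rho of 0 or 0.7.

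**1. Variance.** Independent daily counts with mean mu and variance phi × mu give a 7-day mean with variance phi × mu/7. A Poisson model with dispersion 1 sets it to mu.

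**2. Correlation.** Overlap alone gives (7 − k)/7 at lag k: 0.86, 0.71, 0.57, 0.43, 0.29, 0.14, then 0. An AR(1) with the same lag-1 value gives 0.40 at lag 6 and 0.34 at lag 7. Summed over all lags:
- true: 1 + 2 × (6+5+4+3+2+1)/7 = 7
- AR(1): (1 + 6/7)/(1 − 6/7) = 13

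**3. Model SE divided by true SD, for a slowly varying contrast.**
- Dispersion fixed at 1: sqrt[(mu × 13)/((phi × mu/7) × 7)] = sqrt(13/phi). This is 3.6 at phi = 1, 1.6 at 5, 1.0 at 13 and 0.5 at 50.
- Dispersion estimated: sqrt(13/7) = 1.36 for any phi.

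**4. Simulation under no effect.** Two communities, piecewise-linear time by community, testing the slope change at the start of the intervention, 300 runs per row. Cells show SE/true SD, with type I error at nominal 5%. The Poisson fits use a Wald test and the log-normal fit a likelihood ratio test.

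| Cases/day | phi | rho | Poisson AR(1), dispersion 1 | Poisson AR(1), dispersion estimated | Log-normal AR(1) |
|---|---|---|---|---|---|
| 30 | 1 | 0 | 3.20 (0%) | 1.16 (2.3%) | 1.16 (1.7%) |
| 30 | 5 | 0 | 1.39 (1.0%) | 1.13 (3.0%) | 1.13 (2.7%) |
| 100 | 5 | 0 | 1.44 (0.3%) | 1.17 (3.0%) | 1.17 (2.3%) |
| 30 | 13 | 0 | 0.89 (8.3%) | 1.16 (2.3%) | 1.16 (1.7%) |
| 30 | 5 | 0.7 | 0.93 (7.0%) | 1.29 (2.7%) | 1.29 (1.7%) |
| 30 | 15 | 0.7 | 0.50 (31.7%) | 1.20 (2.3%) | 1.15 (1.3%) |
| 100 | 20 | 0.7 | 0.41 (39.7%) | 1.20 (2.7%) | 1.17 (2.3%) |
| 100 | 50 | 0.7 | 0.31 (51.3%) | 1.41 (0.7%) | 1.39 (0.7%) |

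Repeats with 1,000 runs gave 3.21 (0%) for the first row and 0.53 (27.7%) for phi = 15 with rho = 0.7, both with dispersion 1. For the last row some Poisson fits failed to converge in the repeat, so that SE ratio rests on 300 runs. Simulated ratios at rho = 0 lie somewhat below the formula, partly because the fitted lag-1 value averaged 0.84 rather than 0.857.

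**5. Likelihood ratio test.** A Poisson GLM with residual-side correlation is fitted by quasi- or pseudo-likelihood, so it has no ordinary likelihood ratio. Estimating the dispersion is also quasi-likelihood. A Gaussian model for log values with autoregressive errors does have a likelihood.

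**6. Unsmoothed alternative.** Quasi-Poisson AR(1) on the daily counts, 1,000 runs per setting, gave SE/SD of 0.94–1.02 and type I error of 5–6% at rho = 0. At rho = 0.7 it gave 0.81–0.88 and 9–11%.

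**The case against.** A reader might infer that the plan fits the averages as Poisson, and that its standard errors are therefore several-fold wrong in either direction. The article does not support that.

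- **Poisson is not stated for the average.** The rule can equally send a non-integer average to the log-normal branch, where the error is mild, conservative, and compatible with a likelihood ratio test.
- **Dispersion is not stated to be 1.** Whether a scale is estimated is a detail that an article may leave to the full plan.
- **Too-small standard errors need more than the article gives.** They require fixed dispersion together with overdispersion or day-to-day autocorrelation that the article does not quantify. Both are plausible for reported cases, but they are assumptions.
- **Rolling is stated for plots only.** Non-overlapping weekly averages would also fit the modelling sentence, and the overlap argument would then fall away. The variance mismatch would remain: with independent days and dispersion 1 the ratio would be sqrt[mu/(phi × mu/7)] = sqrt(7/phi), or 2.6 at phi = 1.
- **Wastewater is not affected by the Poisson point.** Its values are continuous, modelled twice weekly and log-transformed.
- **The analysis is labelled descriptive.**

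The first five limit the claim and are accepted. The last does not dispose of it: the Analysis plan still sets a test at 0.05 for every pair, and a descriptive contrast also needs a sound standard error. Nor is this only missing detail, because every branch examined on rolling averages is miscalibrated.

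**Conclusion.** The point holds in conditional form. If the model uses the rolling averages described for the plots, an AR(1) misstates their correlation, and the calibration of the primary comparison depends on choices that the article leaves open.

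- **Poisson, dispersion fixed at 1:** the SE is about 3.2–3.6 times too large at phi = 1 with independent days. It is 0.3–0.5 of the true value at phi = 15–50 with rho = 0.7, where type I error is about 28–51%. The named test is not available for this model.
- **Dispersion estimated, or log-normal:** the SE is 13–41% too large and type I error is 0.7–3%. That is mild, but it costs precision in a study that already declares its power insufficient.

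These sizes rest on order 1, the assumed phi, rho and case levels, and a simplified model without the vaccination and variant covariates. The article does not establish which branch applies.

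**What to change.** 1. Keep 7-day averages for plots only.
2. Model the unsmoothed daily counts with day-of-week terms, or non-overlapping weekly totals, using a negative binomial or quasi-Poisson model with log link and estimated overdispersion.
3. State how the remaining autocorrelation is handled, by a latent autoregressive term or autocorrelation-robust standard errors, and check it by simulation. A plain AR(1) quasi-Poisson fit to daily counts is not enough by itself, given its 9–11% type I error at rho = 0.7.
4. Report interval estimates for the interaction contrasts. Replace the likelihood ratio test with a Wald or robust test, or use a full-likelihood model for which it is valid.
5. Leave wastewater as twice-weekly log-transformed values.

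The cost is revised wording and code and slightly more modelling work. The case data are already collected daily.

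### Hospitalizations, hospital census and ICU admissions are analysed over the same period boundaries and knots as cases, with no lag, so their trend contrast is mis-timed and biased in a direction that depends on the effect's shape

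*Protocol article*

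**What the plan says.** All of this is in the protocol article.

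- **Periods.** The Analysis plan section sets the first boundary by the programme's calendar: "Pre-intervention is defined as from January 1, 2021, until the start date of test kit distribution in each community". The Test distribution section gives the dates: "Test kit distribution began in Pitt County on April 4, 2021, and Hamilton County on May 4, 2021". The intervention period is about 11–12 weeks, and 90 days of post-intervention follow-up come after it.
- **Delay allowance.** The only one is a single week at the end of the intervention period, for households that use their kits late. It is not an outcome lag.
- **Model.** One specification covers everything: "for each outcome and intervention/control community matched pair, a generalized linear model of 7-day average or twice-weekly outcomes by community and time". The knots are placed by period: "Four knots will be considered: at the beginning, at the transition from one period to the next, and at the end". The alternative time model breaks at the same places: "Piecewise linear splines by period will also be considered for adequate fit".
- **Contrast.** "Each intervention community will be compared to each matched control community separately within the intervention periods". The test is made by "comparing the appropriate time-by-community interaction parameters using a likelihood ratio test with alpha = 0.05".
- **Outcomes covered.** Table 2 lists three hospital measures among the secondary outcomes: "Number of new hospitalizations for COVID-19 disease per day", hospital census, and ICU admissions of SARS-CoV-2-positive patients.

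**The concern.** Home testing can lower admissions only by first preventing infections, and an admission follows the infection behind it. Admissions early in the intervention window therefore come from infections acquired before any kit could have mattered. Admissions early in the post-intervention window come from infections acquired while the programme was running. Both time models named in the plan bend at the programme dates, so neither can place the change in the hospital series where it would occur.

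At stake is the reading of the hospital trend contrasts. The abstract lists hospitalizations among the trends used to assess impact, and each contrast is to be tested at 0.05. A reader given the in-period interaction for admissions could not tell whether it is too small or too large. If a lag were chosen only after the curves had been seen, that choice would be driven by the data.

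**Working it through.** **The plan's own figure.** Distribution of 6–7 weeks, plus 4 weeks of testing, plus 1 week for late use: 6 + 4 + 1 = 11 and 7 + 4 + 1 = 12 weeks. This reproduces the stated 11–12 weeks, so D = 77 to 84 days.

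**Inputs from the article.** The pre-period from January 1 is 31 + 28 + 31 + 3 = 93 days to April 4 (North Carolina) and 31 + 28 + 31 + 30 + 3 = 123 days to May 4 (Tennessee). The post-period is 90 days.

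**Assumptions.** The extra lag L of hospital outcomes is 7, 14 or 21 days; the article states none. The series is the noise-free difference, intervention minus control, on the log scale. The interaction is read as a separate linear trend difference in each period.

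**Share of the intervention window before any lagged effect, L/D.** 7 days: 8–9%. 14 days: 17–18%. 21 days: 25–27%.

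**Joint three-segment fit with unshifted knots.** With t in days from the start of distribution, the fitted model is

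d(t) = b0 + b1·t + b2·max(t, 0) + b3·max(t − D, 0).

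The in-period slope is b1 + b2 and the post-period slope is b1 + b2 + b3. The effect shapes, each shifted later by L, are:

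- gradual and held: min(max((t − L)/D, 0), 1);
- gradual, then fading to zero over 30 days;
- a step that is held.

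Each ratio is the lagged in-period slope divided by the zero-lag in-period slope. Ranges run over both states and both values of D.

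| Effect shape | L = 7 | L = 14 | L = 21 |
|---|---|---|---|
| Gradual, held | 0.97–0.98 | 0.92–0.94 | 0.84–0.88 |
| Gradual, fading | 1.14–1.17 | 1.22–1.26 | 1.23–1.28 |
| Step, held | 1.21–1.28 | 1.38–1.52 | 1.50–1.70 |

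For the gradual, held shape the true slope outside the intervention segment is zero. The fit nevertheless gives a post-period slope of about 8–9%, 19% and 30% of the true in-period slope at the three lags, and a pre-period slope of the opposite sign of about 4–13%. An effect that steps up and then switches off has a zero-lag slope near zero in some settings, so its ratio is not informative and is left out.

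**Four-knot restricted cubic spline.** For the gradual, held shape, the fitted change over the intervention period is 0.97–0.99, 0.93–0.96 and 0.87–0.90 of its zero-lag value. For a held step it is above 1. The pattern is the same as for the piecewise-linear model.

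**Effect of the repair.** With both inner knots shifted by L, the gradual, held slope returns to 1.00. The fading and held-step ratios come down to about 1.03–1.15. They do not reach 1 exactly because a straight segment does not fit those shapes and the post-period is cut short by L.

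**The case against.** The strongest points on the other side are these.

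- **A reader might infer that any programme effect on admissions is diluted toward no effect.** The documents do not support that. Dilution is assured for a contrast of mean levels: a held step keeps only 0.91–0.92, 0.82–0.83 and 0.73–0.75 of its mean level at the three lags. The plan compares trend parameters, and for those the table shows ratios on both sides of 1. The objection stands in full.
- **A reader might also put the loss at 13–40%.** Fitting a single line through the origin over the intervention window gives ratios of 0.864, 0.730 and 0.601 for D = 77, and 0.875, 0.752 and 0.633 for D = 84. That treats the level and trend at the start as known and drops the post-period. The plan models all periods together, and there the loss for the same shape is 2–16%.
- **Cases also lag infection.** This is true: only the extra delay of hospital outcomes separates them from cases, and its length is an assumption.
- **The article condenses a fuller plan, and the knots are only under consideration.** A lag rule may exist elsewhere. But the article does more than stay silent. It gives one model for every outcome and names two time models, both tied to programme dates, so neither option allows a lag.
- **Late effects are kept and the analysis is called descriptive.** The 90 days of follow-up and the plots would show a delayed effect, which limits the harm. They do not correct the in-period contrast, which is tested at 0.05. The descriptive label lowers the severity without removing the point.

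**Conclusion.** The point holds as a mis-timing of the trend contrast for three secondary outcomes, with bias of uncertain direction. For an extra lag of 7 to 21 days, a gradual, sustained effect has its in-period slope understated by about 2–16% and leaves a false post-period slope of about 8–30% of the true one. A fading or step effect is overstated, by ratios of about 1.1 to 1.7.

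These sizes rest on the assumed lags, the assumed effect shapes, noise-free series and the piecewise-linear reading of the interaction. They illustrate what the rule can do and are not estimates for this study. Severity is minor.

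**What to change.** For new hospitalizations, hospital census and ICU admissions, prespecify a lag with its justification, and shift both inner knots and both period boundaries by it. At the least, prespecify a sensitivity analysis that shifts both by 0 to 21 days and reports how the trend contrast changes. Keep the unshifted dates for mobility, where a behavioural response need not wait for admissions.

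The cost is a few sentences in the analysis plan and some repeat model fits. There are two downsides. The lag is an assumption to defend, which reporting the whole range eases. The hospital post-period also falls by the lag, from 90 to as few as 90 − 21 = 69 days, unless the data are drawn correspondingly longer.
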